**Study Protocol for the Real-world E-Consumer Cohort of pre-exposure prophylaxis (RECOPE) in China**

1. **Rationale of the study**

HIV/AIDS remains a major public health challenge in China and worldwide. According to the Joint United Nations Programme on HIV/AIDS (UNAIDS), 39.9 million people are living with HIV globally in 2023, with approximately 1.5 million new infections reported that year [1]. In China, over 1.2 million individuals were living with HIV by the end of 2022, and more than 107,000 new infections were reported in the same year [2]. The epidemic continues to disproportionately affect vulnerable populations such as men who have sex with men (MSM) and sex workers.

Pre-exposure prophylaxis (PrEP) is a proven biomedical prevention tool that reduces the risk of HIV acquisition through sexual contact by up to 99% when taken correctly [3]. Two main PrEP regimens are available: (1) the daily regimen, recommended for all high-risk populations, which involves taking one pill daily; and (2) the event-driven (ED) regimen, also known as “2-1-1,” recommended for MSM, which involves 2 pills 2–24 hours before sex, followed by 1 pill 24 hours and 48 hours later. The World Health Organization and Chinese Expert Consensus both strongly recommend PrEP for individuals at high risk of HIV[4,5]. PrEP is officially approved in China in 2020, marking an important step toward HIV prevention scale-up.

With the rapid development of internet hospitals and online health platforms, new pathways for PrEP access have emerged. Online platforms offer discreet and convenient services, reducing barriers related to stigma and healthcare access. For MSM and other key populations, online purchase of PrEP may overcome barriers encountered in traditional clinic settings. However, unlike face-to-face clinical services, online platforms may lack structured mechanisms for adherence counseling and follow-up.

In China, BluedHealth, a leading internet-based health platform, has become a major channel for PrEP distribution. In 2023, BluedHealth reported an average of over 3,000 PrEP sales per month, reflecting increasing acceptance of online PrEP services. Despite this expansion, there is little evidence regarding adherence patterns and associated factors among real-world online PrEP consumers in China[6].

To address this gap, the Real-world E-Consumer Cohort of pre-exposure prophylaxis (RECOPE) is established as the first prospective cohort study targeting individuals purchasing PrEP online in China.

1. **Study Objective:**
2. **Primary Objective**

To evaluate medication adherence among real-world e-consumers of PrEP in China, with a focus on both event-driven (ED) and daily regimens, over baseline and three follow-up visits (1, 3, and 6 months), to identify socio-demogrphic and psycho-behavioral factors associated with PrEP adherence, including self-efficacy, PrEP-related stigma, depressive symptoms, and sexual behaviors (e.g., number of partners, chemsex, condom use, sexual role), and to provide evidence to inform interventions that optimize real-world PrEP effectiveness.

1. **Secondary Objectives**

- To assess the utilization of other HIV-related services (e.g., willingness to use long-acting injectable PrEP, HIV testing behavior)
- To evaluated the factors associated with the utilization of other HIV-related services.

1. **Study Design and Methodology**

**3.1 Study Design**

This study is a prospective cohort study designed to follow real-world e-consumers of pre-exposure prophylaxis (PrEP) in China. Eligible participants who purchased PrEP through BluedHealth, the largest internet-based platform for PrEP distribution in China, will be enrolled. Participants will complete a baseline survey and follow-up assessments at 1, 3, and 6 months.

**3.2 Sample Size Calculation**

The required sample size is calculated using Cochran’s formula for estimating a single population proportion, incorporating finite population correction and a design effect adjustment, as shown in Equation (1). Based on previous studies, we assumed an optimal adherence prevalence of 60%, a two-sided significance level of α = 0.05, and a desired precision (margin of error) of 5%.

A design effect (deff) is included to account for potential clustering introduced by the recruitment workflow, since participants will be conveniently recruited by the designated recruiters through the same platform channels may share unobserved similarities. Following the standard formula deff = 1 + (m – 1) × ICC, we assumed an average cluster size of approximately 11 participants per recruiter and a small intraclass correlation coefficient (ICC) of 0.01. This yielded deff ≈ 1.1, which is applied as a conservative adjustment [7,8].

In addition, a 15% anticipated loss to follow-up is included. The final minimum required sample size is calculated to be 424 participants using PASS software.

n = deff × [N p̂ q̂] / [(d² / 1.96²)(N – 1) + p̂ q̂] (1)

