**Primary Outcome**

The primary outcome of this study is PrEP adherence, assessed separately for daily and event-driven (ED) regimen users at each follow-up visit (1, 3, and 6 months after baseline).

- **ED users:** Adherence to ED regimen is assessed by four items. First, the participants are asked whether they had engaged in sexual activity in the past one and three months, respectively (the 1-month follow-up survey only asked this question for the past one month). Those who answer “no” or reported to have never initiated PrEP in a previous question were treated as missing data for PrEP adherence. Those who answer “yes” are then asked if they had taken PrEP for each sexual encounter in the corresponding time period, including those with both primary (e.g., main or long-term partners) and non-primary (e.g., casual or commercial partners) sexual partners (1 = every time, 2 = sometimes, and 3 = never). The participants who choose “every time” or “sometimes” are subsequently asked three adherence questions based on the ‘2-1-1’ dosing guideline: (i) whether (yes or no) they took two pills of PrEP 2 to 24 hours before the sexual activity for each medication (timepoint A); (ii) whether they took one pill 24 hours after the first dose for each medication (timepoint B); and (iii) whether they took another pill 48 hours after the first dose for each medication (timepoint C). The participants who reported to take PrEP for each sexual encounter and chose “yes” to all three adherence questions are classified as “being adherent,” otherwise, they would be classified as “non-adherent.” Lastly, three binary outcome variables are constructed: past 1-month adherence based on baseline and all follow-up data, past 3-month adherence based on baseline and 3- and 6-months follow-up data, and consistent adherence based on 3- and 6-months follow-up data (defined as having optimal past 3-month adherence at both 3- and 6-month follow-up surveys).
- **Daily users:** Adherence to daily PrEP regimen is assessed with a single item: “In the past month, have you ever failed to take PrEP on time and in a correct dosage? (yes/no).” Participants who answer “no” are classified as “adherent,” and those who chose “yes” are categorized as “non-adherent”

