**Descriptive Analyses**

- **Baseline characteristics:** Continuous variables (e.g., age, psychosocial scores) will be summarized as means (standard deviations) or medians (interquartile ranges), depending on distribution. Categorical variables (e.g., education, income category, sexual role) will be summarized as frequencies and percentages.
- **Adherence prevalence:** The prevalence of optimal PrEP adherence at each wave will be calculated separately for ED and daily users.
- **Scale Reliability:** Internal consistency of psychosocial measures (e.g., PHQ-9, self-efficacy scale, stigma scale) will be evaluated at baseline using Cronbach’s alpha. Alpha values ≥0.80 will be considered acceptable.

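### The ±5-point precision in section 3.2 is computed for one pooled adherence proportion and is not secured for the regimen-specific primary outcome

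*Protocol*

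**What the plan says.** Section 3.2 uses a formula "for estimating a single population proportion". Its inputs are 60% adherence, "a two-sided significance level of α = 0.05", "and a desired precision (margin of error) of 5" per cent, a finite population correction, a design effect of 1.1 and 15% loss to follow-up. The result is one minimum total of 424, with no regimen split or quota. Equation (1) contains N, but the section gives no value for it.

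The Primary Outcome part of section 3.6 states: "The primary outcome of this study is PrEP adherence, assessed separately for daily and event-driven (ED) regimen users at each follow-up visit". The two regimens use different instruments: a multi-item check against 2-1-1 dosing for ED users (past one or three months), and a single past-month item for daily users. For ED users, those reporting no sexual activity in the recall period and those who "reported to have never initiated PrEP in a previous question were treated as missing data for PrEP adherence" drop out of the denominator.

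The Descriptive Analyses in section 3.8 state: "The prevalence of optimal PrEP adherence at each wave will be calculated separately for ED and daily users". The Regression Analyses in the same section also model the regimens separately. Section 3.4 recruits against a threshold of 650, which is not linked to 424.

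**The concern.** The ±5 points in section 3.2 is attached to a quantity that no planned analysis produces. A reader would naturally take it as the precision of the primary outcome. Once the sample is divided between two regimens, each prevalence rests on only part of it. The ED part shrinks again at each wave, through missingness that section 3.2 does not allow for. The primary objective covers both regimens, so the loss of precision in the smaller group matters: its margin could be roughly double the stated one.

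**Working it through.** **Inputs from section 3.2.** p = 0.60 ("we assumed an optimal adherence prevalence of 60" per cent), q = 0.40, z = 1.96, d = 0.05, loss 15%. Design effect: 1 + (11 − 1) × 0.01 = 1.1 ("This yielded deff ≈ 1.1, which is applied as a conservative adjustment"). The threshold of 650 is from section 3.4.

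**Assumptions.** N is about 3,000, inferred from the monthly sales figure in section 1. Regimen splits run from 50:50 to 80:20, since none is stated. ED missingness (no sex or PrEP not initiated) is 10–20%, since none is stated. p = 0.60 applies in both regimens.

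**Step 1: reproduce 424.** With N = 3,000, d²/1.96² = 0.0025/3.8416 = 0.000651.

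- Equation (1) before the design effect: 3,000 × 0.24 / (0.000651 × 2,999 + 0.24) = 328.5.
- Times 1.1 = 361.4; divided by 0.85 = 425.1, rounded up to 426.
- With N = 2,900: 360.0/0.85 = 423.5, rounded up to 424.
- Without the correction: 0.24 × 3.8416/0.0025 = 368.8; × 1.1 = 405.7; /0.85 = 477.3, which does not match.

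So 424 is one total for one proportion, with the finite population correction applied.

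**Step 2: pooled half-width after loss.** Half-width = 1.96 × √[1.1 × 0.24/n × (N − n)/(N − 1)]. The last factor is dropped for the uncorrected figure.

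- 424 enrolled, n = 360.4: ±5.30 uncorrected, ±4.98 corrected.
- 650 enrolled, n = 552.5: ±4.28 uncorrected, ±3.87 corrected.

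**Step 3: half-width by regimen.** If a regimen has share s of both sample and population, its half-width is very nearly the pooled one divided by √s. For example, at 424 and 50:50: 4.98/√0.5 = 7.0 and 5.30/√0.5 = 7.5. Entries below are in points, at follow-up, with to without correction, before ED missingness.

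| Enrolled | Split | Larger regimen | Smaller regimen |
|---|---|---|---|
| 424 | 50:50 | 7.0–7.5 | 7.0–7.5 |
| 424 | 70:30 | 5.9–6.3 | 9.1–9.7 |
| 424 | 80:20 | 5.6–5.9 | 11.1–11.9 |
| 650 | 50:50 | 5.5–6.1 | 5.5–6.1 |
| 650 | 70:30 | 4.6–5.1 | 7.1–7.8 |
| 650 | 80:20 | 4.3–4.8 | 8.7–9.6 |

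**Step 4: share needed for ±5 at follow-up.** The share is (pooled half-width/5)².

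- At 424: (4.98/5)² = 0.99 corrected; (5.30/5)² exceeds 1 uncorrected, so ±5 is out of reach.
- At 650: (3.87/5)² = 0.60 corrected; (4.28/5)² = 0.73 uncorrected (73.5% when solved directly, so about 74%).

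**Step 5: ED missingness.** Uncorrected half-widths grow by 1/√0.9 = 1.05 or 1/√0.8 = 1.12. With 424 enrolled and a 70% ED share, 6.3 becomes 6.7 or 7.1.

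**The case against.** The strongest reply is that 424 is only a minimum and that recruitment works to 650. A reader might infer from the mismatch that ±5 points fails in both regimens whatever happens. The documents do not support that. At 650 the larger regimen reaches ±5 once its share is about 60% (corrected) or 74% (uncorrected). With an 80% ED share and N near 3,000, the corrected ED margin is about ±4.6 to ±4.9 even with 10–20% missing. Baseline estimates carry no loss to follow-up, so they are tighter. At 424, a regimen with at least 82% of the sample meets ±5 at baseline with correction. All of this stands, but the primary outcome is defined at the follow-up visits, and the smaller regimen still falls short there.

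A reader might also infer that the two outcomes cannot be pooled. Both regimens yield a binary past-month status, so a pooled proportion could be computed. The text shows only that none is planned.

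The design effect would be somewhat smaller within a regimen. At 1.0, one regimen would still need at least 90% of 424 to reach ±5 after loss, and at 650 an even split would still give 5.47/√1.1 = ±5.2 corrected.

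Finally, no test or decision rule depends on ±5 points, so the mismatch is no ground for demanding more participants. A separate analysis plan, however, could not change what 424 was computed for.

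**Conclusion.** The point holds in this form: section 3.2 does not secure ±5 points for the regimen-specific primary outcome. At 424 with the planned 15% loss, neither regimen reaches it at follow-up under a realistic split. At 650 the larger regimen may reach it, depending on its share, and the smaller one does not (±5.5 to ±6.1 at best, at 50:50). ED missingness widens the ED margins further and is not budgeted for.

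That the target does not match the outcome is plain from the text and needs no assumption. The sizes rest on 60% adherence in both regimens, a design effect of 1.1, an inferred N of about 3,000 and assumed splits. The uncorrected ends of the ranges cover any larger N, which would apply if recruitment is widened to earlier purchasers. This is a defect in the stated justification, and it does not invalidate the planned analyses.

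**What to change.** In section 3.2, state that ±5 points applies only to a pooled adherence proportion and not to the regimen-specific primary outcome. Add a small table of the expected half-width for ED and for daily users at 424 and at 650, using the protocol's own formula with the finite population correction. State the value of N, the assumed regimen split and the assumed fraction of ED users with no sexual activity or no PrEP initiation.

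The cost is one rewritten paragraph and one table. No enrolment target, outcome definition or analysis changes. The only downside is a less favourable stated precision.

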**3.4 Recruitment Procedure**

Recruitment will be conducted in collaboration with BluedHealth. Staff from BluedHealth will distribute recruitment materials (texts and posters) containing a unique identification key and contact details. The unique keys will be generated using a four-digit code plus a letter (e.g., 1001c, 1002d), ensuring each participant can be individually tracked.

The first round of recruitment will target individuals who purchased PrEP within one month prior to study initiation. If fewer than 650 participants are enrolled within two weeks, subsequent rounds will expand eligibility to those who purchased PrEP within the past two or three months, until the target sample size is reached (ideally within 30 days).

Recruiters will contact eligible clients through BluedHealth customer service channels or directly at the time of PrEP purchase, inviting them to join the study. Interested individuals will scan a WeChat QR code to connect with study investigators. Prospective participants must include their unique key when adding the investigator to confirm identity. Investigators will verify inclusion/exclusion criteria, obtain informed consent, and finalize enrollment.

A reminder mechanism will be implemented: after receiving the QR code, potential participants will receive up to two reminders within 48 hours. If they do not respond, the key will be invalidated. Each participant’s unique key will serve as their identifier throughout the study(figure 1).

[figure not shown]

Figure 1 Flowchart of the study procedure

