**3.7 Data Management and Quality Control**

Survey responses are automatically recorded on the Wenjuanxing platform and exported as encrypted files. All datasets are stored on password-protected institutional servers, accessible only to authorized study staff. Each participant is assigned a unique identifier at recruitment, which is used throughout all surveys to ensure anonymity. No personal identifiers are collected or stored.

To ensure data quality, each submission is reviewed for completeness, internal logic consistency, and reasonable completion time. Submissions failing these checks are excluded from analysis and do not qualify for incentives. Logic constraints are built into the questionnaire to minimize careless or contradictory responses.

During data management, double validation procedures are applied at the time of dataset export and cleaning. Backup copies are securely maintained, and audit trails are preserved to document data handling. All analytic datasets used for statistical analyses will be fully anonymized.

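### The minimum of 424 allows only for 15% loss to follow-up, so at follow-up it has no reserve for the other outcomes that the protocol's own rules remove

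*Protocol*

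**What the plan says.** Protocol section 3.2 sizes the study for one proportion, with assumed adherence of 60%, two-sided α of 0.05 and a margin of 5 points. It uses Cochran's formula with finite population correction and a design effect: "This yielded deff ≈ 1.1, which is applied as a conservative adjustment". It then states that "a 15% anticipated loss to follow-up is included" and arrives at a minimum of 424. It gives no value for the population size N.

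Other sections determine who contributes an outcome:

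- Section 3.6, Primary Outcome, ED users: those reporting no sexual activity in the window, or who never started PrEP, "were treated as missing data for PrEP adherence". The item for daily users has no such rule.
- Section 3.7: "Submissions failing these checks are excluded from analysis".
- Section 3.8: complete cases, no imputation, with the expectation that missing data come mainly from loss to follow-up.

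Section 3.4 uses a different number: "If fewer than 650 participants are enrolled within two weeks", the purchase window is widened, and recruitment goes on until the target is met. The section does not say how 650 relates to 424.

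**The concern.** An ED user with no sex in the window, a person who bought PrEP but never took it, and a respondent whose submission fails the checks have not been lost to follow-up. Even so, none of them yields an adherence outcome. Never-initiators can be enrolled, because section 3.3 asks for a purchase and a plan to use PrEP, not for initiation. The 15% allowance does not cover these groups, and the complete-case approach does not restore them.

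What is at stake is the precision claim attached to 424. If the number is only just large enough after 15% loss, it cannot also absorb these removals at the follow-up visits, which is where section 3.6 places the primary outcome. With 424 in one section and 650 in another, a reader also cannot tell which number carries the ±5 points.

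**Working it through.** **Inputs.** From section 3.2: p = 0.60, q = 0.40, d = 0.05, multiplier 1.96, deff = 1 + (11 − 1) × 0.01 = 1.1, loss 15%. Assumed: N = 3,000, borrowed from the monthly sales figure in section 1. Those are sales rather than persons, so other values of N are shown. Also assumed: x, the share of retained participants whose outcome is removed by the section 3.6 and 3.7 rules.

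**Reproducing 424.** Equation (1) at N = 3,000:

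n = 1.1 × (3000 × 0.24) / [(0.05² / 1.96²) × 2999 + 0.24] = 1.1 × 720 / 2.1917 = 361.4

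361.4 / 0.85 = 425.1, close to 424. N between about 2,900 and 2,926 gives exactly 424. Leaving out both the correction and the design effect and multiplying by 1.15 also gives it (368.8 × 1.15 = 424.1), but that would not be the stated method.

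**Requirement under other N.** N = 6,000 gives 382 and N = 9,000 gives 390. These are relevant because section 3.4 allows the purchase window to grow to two or three months. Without the correction the figure is 406.

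**Reserve at follow-up.** 424 × 0.85 = 360.4 outcomes against 361.4 required at N = 3,000. There is no slack, and with larger N there is already a deficit.

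**Margin reached with 424 after 15% loss and further removal x.** Outcomes n = 424 × 0.85 × (1 − x). Margin = 1.96 × √[0.24 × 1.1 / n × (N − n/1.1)/(N − 1)], the last factor being dropped without the correction. Enrolment needed for ±5 = required n / [0.85 × (1 − x)].

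| x (assumed) | Outcomes | Margin, N = 3,000 | Margin, no correction | Enrolment for ±5, N = 3,000 | Enrolment for ±5, no correction |
|---|---|---|---|---|---|
| 0% | 360.4 | ±5.01 | ±5.30 | 426 | 478 |
| 5% | 342.4 | ±5.15 | ±5.44 | 448 | 503 |
| 10% | 324.4 | ±5.31 | ±5.59 | 473 | 531 |
| 20% | 288.3 | ±5.67 | ±5.93 | 532 | 597 |
| 30% | 252.3 | ±6.09 | ±6.34 | 608 | 682 |

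**Baseline.** With no loss to follow-up, 424 with 15% removed leaves the same 360.4 outcomes and ±5.01. Baseline therefore tolerates about 15% removal at N = 3,000.

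**What 650 would absorb.** 650 × 0.85 = 552.5. Further removal tolerated for a pooled ±5 is 1 − 361.4/552.5 = 34.6% (N = 3,000) or 1 − 405.7/552.5 = 26.6% (no correction).

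**By regimen.** Sections 3.6 and 3.8 report ED and daily users separately. With an assumed 50/50 split, 15% loss, no correction and no further removal:

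- 424 gives 180.2 per regimen, and 1.96 × √(0.264/180.2) = ±7.5 points.
- 650 gives 276.3 per regimen, and 1.96 × √(0.264/276.3) = ±6.1 points.

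**The case against.** The strongest reply is that 424 is a minimum, not a stopping point. No section tells recruitment to halt there, and section 3.4 most naturally reads as a target of 650, about 53% above 424. A reader might infer that the study will stop at 424 and miss its precision; the protocol does not say so. This stands, and it reduces the practical risk. It does not repair section 3.2, which attaches ±5 points to 424, or supply the missing link between the two numbers.

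A reader might also take the size of the shortfall as established. It is not. No removal rate is given, and at 5% the effect is about a tenth or two of a point. Section 3.8 expects missing data mainly from loss to follow-up. The 20% and 30% rows correspond to 17% and 25.5% of those enrolled (0.20 × 0.85 and 0.30 × 0.85), more than the 15% loss, so they run against that expectation. The no-sex and never-initiated rules appear only for ED users, whose share is not stated, and eligibility requires high risk and an intention to use PrEP. Large rates are therefore possible but not indicated. What survives is the direction: with no reserve at follow-up, any positive rate exceeds the margin.

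Finally, 361 might be read as the correct requirement. It depends on an N that section 3.2 does not give, so it should not be written into the plan. Nor is 424 a miscalculation: the stated method reproduces it at a plausible N.

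**Conclusion.** The point holds in a limited form. Section 3.2 omits losses that sections 3.6 and 3.7 prescribe, and 424 has no reserve for them at the follow-up visits: about 360 outcomes against 361 (N = 3,000), 382 (N = 6,000) or 406 (no correction). The excess over 5 points depends on assumed rates. It runs from about 0.2 points at 5% extra removal to 1.1 at 30% with N = 3,000, and from 0.4 to 1.3 without the correction. All of this concerns the pooled proportion on which the formula is built. Enrolling 650 would probably protect that pooled margin, but neither 424 nor 650 gives ±5 points for both regimens under an even split. This should be corrected; it does not threaten the conduct of the study.

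**What to change.** In section 3.2:

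- State N and its source.
- Express the requirement as the number of scored adherence outcomes at a visit.
- Inflate for loss to follow-up, outcomes missing by the section 3.6 rule and quality-check exclusions, using a stated expected evaluable share.
- Say that the ±5 points refers to the pooled proportion, and add the expected ED/daily split with the resulting margin for each regimen.

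In sections 3.2 and 3.4, state that 650 is the enrolment target and how it relates to the minimum. If 424 is kept as the minimum, restate its follow-up margin as above 5 points and list the assumptions.

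The cost is a few sentences and a recalculation. Nobody beyond the 650 already foreseen need be enrolled, unless the stated N and evaluable share turn out to require more: the table's least favourable case, 30% removal without the correction, needs 682. The other cost is a less favourable stated margin for 424 and for each regimen.
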